## Methods/design

### Aims and research questions

There are two aims of this study:To assess the effectiveness of the CHIP intervention in reversing abnormal fasting blood sugar levels in people with T2DM.To determine the cost benefit of the CHIP intervention for persons with a diagnosis of T2DM.

The study will address three main questions;

In a diabetic population within a general practice group on the Central Coast of New South Wales, Australia:When compared to a control group receiving routine diabetic care, what changes occur in fasting blood sugar levels (FBSL), HBA1c, fasting lipogram with triglycerides (FLT), blood pressure (BP), abdominal girth, body mass index (BMI) and medication use among  individuals participating in the CHIP intervention delivered over a period of 12 weeks with additional monthly follow up for another 9 months?Over a 12-month period, what levels of compliance with the intervention are observed in participants?When compared to routine diabetic care, what is the cost benefit (over a 12-month period) of implementing a CHIP intervention delivered over a period of 12 weeks with an additional follow up for another 9 months?

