### Allocation of participants to a study group

Invitees who are willing to participate will be recorded on a list until such time as there are between 30 and 40 individuals listed. At this point, the individual participants will be randomized into either Group 1 or Group 2.

Once allocated, participants in Group 1, will receive the CHIP intervention over a period of 12 weeks. At the end of the 12 weeks period, Group 1 will receive monthly follow-up for a further 9 month period. This process will be repeated, until the full number of participants have been collected and assigned.

An overview of the study design and allocation of participants is illustrated in Fig. 1.

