### Interventions

#### Group 1- intervention group

All participants in Group 1 will participate in the CHIP intervention for 12 weeks. The CHIP intervention consists of 18 education sessions, each of 90 min duration. Approximately half of each session is devoted to viewing pre-recorded visual material delivered by lifestyle medicine professionals, while interactive group discussions and activities, including food preparation and exercise demonstrations delivered by CHIP trained volunteers, make up the remaining time. An outline of the topics covered over the 18 sessions can be viewed in Table 1.

**Table 1 Tab1:** CHIP sessions as per topic

Session number	Topic
1	The rise of chronic disease
2	Lifestyle as medicine
3	The common denominator of chronic disease
4	The optimal lifestyle
5	Eat more, weigh less
6	Fibre, your new best friend
7	Disarming Diabetes
8	The heart of the matter – heart healthy
9	Controlling blood pressure and discovering protein
10	Bone health essentials
11	Cancer prevention
12	Understanding your results and taking action
13	Become what you believe. Your DNA is not your destiny
14	Practicing forgiveness
15	Re-engineering your environment
16	Stress relieving strategies
17	Fix how you feel
18	From surviving to thriving

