Sessions 1 to 11 provides information on the aetiology, risk factors and pathological mechanism responsible for lifestyle related chronic disease. Emphasis is placed on the links between obesity, diabetes, hypertension, hyperlipidaemia and cardiovascular disease. Participants are provided with information relating to how lifestyle changes, particularly in diet and levels of physical activity, can positively alter the risk factors for as well as the course of chronic diseases. Specifically, the adoption of a plant-based, restricted sugar and salt diet is encouraged as well as daily physical activity involving a combination of aerobic and strengthening exercise most days of the week. Sessions 12 to 18 provide information related to other important lifestyle behaviors like substance use, rest, and sleep and stress management. Participants are provided with strategies that will assist them in assuming a position of control of their health, to overcome barriers, to manage and maintain behavior change and to cope with environmental pressures and stressors. At the end of the 12-week program, participants will be contacted for the purpose of assessing compliance and providing motivation and support on a monthly basis for an additional 9 months. Participants who receive less than 80% (4 sessions) of the program content will be regarded as having dropped out from the intervention and therefore will be excluded from the study. Self reported reasons for dropout will be noted.

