#### Group 2 – control group

The control group will continue to receive their usual diabetes care and not receive any intervention or details about the CHIP intervention.

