### Statistical analysis

All data collected will be coded and entered into IBM® SPSS® version 22 for Windows® (SPSS Inc., 2013) before analysis.

#### Analysis for research question 1 and 2

Descriptive statistics will be used to analyze demographic data, anthropometric measurement data, blood results and activity levels on commencement of the program and also at the described re-evaluation intervals. Descriptive statistics will include frequencies, percentage distribution, means, and medians as well as standard deviation from the mean.

The Shapiro-Wilk test will be used to determine normal distribution to decide on whether to use parametric or non-parametric testing for correlations and variance analysis. A paired sample t-test (dependent t-test) will be used to compare pre intervention data with post intervention (12 weeks) and pre intervention data with post intervention (12 months) data. An independent t-test will be used to compare data between intervention and control groups. Pearson’s correlation will be used to explore relationships between continuous variables. The dietary inventory, health survey, and quality of life survey will be independently scored and the results between groups compared using linear regression. The level of significance is set at *p* < 0.05.

#### Analysis for research question 3

To determine the cost benefit of the intervention, a cost-benefit analysis will be undertaken. The cost benefit analysis will involve assessment of beneficial effects of the intervention. The analysis will include benefits and costs attributed to the project and indirect costs. Therefore, where B represents all the benefits and C represents all the costs, the project will be considered beneficial if B-C > 0. A cost benefit ratio will also be calculated. Costs included in the analysis will include opportunity costs. Costs from published literature and from government agencies will be used wherever possible, for example, the Medical Benefits Scheme and Pharmaceutical Benefits Scheme.

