### Limitations

Several factors may influence the results obtained in this study. Firstly, compliance with the intervention is paramount to the success of lifestyle modification programmes, but it is also difficult to measure actual compliance reliably. Some data collection, namely dietary analysis, exercise compliance and medical costs will rely on patient integrity and accurate reporting which may not necessarily be reliable.

A potential confounder is that of the Hawthorne effect in that the participants’ behaviour may be affected by the fact that data is collected at baseline and again at future intervals.

The outcomes of this study have the potential to inform decisions about patient treatment and potentially provide incentive for the provision of funded lifestyle- based preventive and restorative programs for patients diagnosed with T2DM.

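### Removing CHIP participants who receive under 80% of the programme from the study, after randomisation and in one arm only, breaks the randomised comparison

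*Protocol article*

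**What the plan says.** The rule is in the description of the intervention group (Protocol article, Group 1- intervention group): "Participants who receive less than 80% (4 sessions) of the program content" are to be "regarded as having dropped out from the intervention and therefore will be excluded from the study". Reasons for dropping out are to be noted. The same section gives the programme's length: "The CHIP intervention consists of 18 education sessions, each of 90 min duration".

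Randomisation comes first (Allocation of participants to a study group): "Once allocated, participants in Group 1, will receive the CHIP intervention over a period of 12 weeks". The control group is to "not receive any intervention or details about the CHIP intervention" (Group 2 – control group).

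The comparison between arms is described in one sentence (Statistical analysis): "An independent t-test will be used to compare data between intervention and control groups". No analysis set is named there, and nothing elsewhere in the article confines the 80% rule to a secondary or per-protocol analysis.

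Research question 2 asks "what levels of compliance with the intervention are observed in participants", over 12 months. Research question 3 asks about cost benefit over the same period.

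**The concern.** The sentence moves from leaving the programme to leaving the study. Those are different events. Someone who stops attending CHIP is still a randomised participant, and that person's glucose at 12 weeks and 12 months is part of the effect of offering CHIP.

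Attendance is behaviour under the assigned treatment, so filtering on it in one arm gives away the balance that randomisation created. The protocol itself holds that "compliance with the intervention is paramount to the success of lifestyle modification programmes" (Limitations). It would therefore be surprising if people who attended 80% or more had the same prognosis as people who did not.

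The article says the results may inform decisions about funding such programmes. A funder pays for everyone enrolled, including those who stop coming. A result in attenders, reported as the result of the programme, would probably overstate what the funder would get. If excluded participants are also not measured, no later analysis can recover their outcomes.

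**Working it through.** **Step 1. Is the exclusion post-randomisation and one-sided?** Allocation precedes the first session, so attendance cannot be known at randomisation. Group 2 has no sessions, so no equivalent criterion can remove a control. Controls may still leave for other reasons, because any participant may exit at any time and a 10% dropout rate is planned. The asymmetry lies in the attendance filter; it does not mean that every control is retained.

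**Step 2. What does the threshold amount to?** 80% of 18 sessions is 0.8 × 18 = 14.4. Fifteen sessions is 15/18 = 83.3% and passes; fourteen is 14/18 = 77.8% and fails. Missing four sessions is therefore the smallest absence that triggers the rule. Read as sessions received, four would be 4/18 = 22.2%, which does not fit 80%.

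**Step 3. How large could the bias be?** The plan has no figure of its own to reproduce here.

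Inputs from the protocol:
- 75 randomised per arm (Study design).
- Significance level 0.05, taken as two-sided (Sample size estimate, which refers to a 95% confidence interval).
- 10% dropout (Sample size estimate). This is the only attrition figure given, and it is not stated to be the exclusion rate.

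Assumed inputs, which the documents do not give:
- The excluded share f of Group 1: 10%, 20% or 30%.
- The correlation r between attendance and better follow-up glucose when CHIP has no effect: 0.2 to 0.4.

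If the lowest fraction f on a normal attendance scale is removed, the mean outcome of those kept shifts by

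shift (in SD) = r × φ(z_f) / (1 − f),

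where z_f is the f-quantile of the standard normal and φ its density. With n = 75(1 − f) kept against 75 controls, SE = √(1/n + 1/75) in SD units, and

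type I error = 1 − Φ(1.96 − shift/SE) + Φ(−1.96 − shift/SE).

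This ignores the slight loss of variance in the selected group.

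| f | φ(z_f)/(1 − f) | n kept | SE | Shift, r = 0.2 to 0.4 | Type I error |
|---|---|---|---|---|---|
| 10% | 0.1755/0.9 = 0.195 | 67.5 | 0.168 | 0.039 to 0.078 SD | 5.6% to 7.5% |
| 20% | 0.2800/0.8 = 0.350 | 60 | 0.173 | 0.070 to 0.140 SD | 6.9% to 12.8% |
| 30% | 0.3477/0.7 = 0.497 | 52.5 | 0.180 | 0.099 to 0.199 SD | 8.6% to 19.7% |

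**Step 4. Check with a different model.** Suppose a share q of Group 1 is excluded and those people would do worse by g SD than those kept. The bias is then q × g. For g = 0.25 to 0.5 SD:
- q = 10%: 0.025 to 0.05 SD, type I error 5.3% to 6.0%.
- q = 20%: 0.05 to 0.10 SD, type I error 6.0% to 8.9%.
- q = 30%: 0.075 to 0.15 SD, type I error 7.0% to 13.2%.

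Simulation of 20,000 trials per scenario at g = 0.5 gave 5.9%, 8.9% and 13.5%. The two models differ in how strongly they tie attendance to outcome, but both show the error rising with the share excluded.

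**Step 5. Effect on the other two questions.** For question 2, the lowest attenders leave the compliance data, and session attendance among those kept is at least 80% because of the rule. For question 3, the later medical costs and the benefits of part-attenders drop out, and possibly their programme costs too.

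**The case against.** The best defence is that the sentence describes the intervention rather than the analysis. Repeat data collection is planned for both groups, the t-test is not expressly limited to completers, and a statistical analysis plan that is not shown might define an as-randomised set. This does not remove the problem. The article positively states exclusion from the study, and nothing in it overrides that. If follow-up stops as well, an as-randomised set would have no outcomes for these people.

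Other objections do stand, and they limit what can be claimed:

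- A reader might infer that the threshold contradicts itself. It does not if the four sessions are sessions missed; 14/18 is indeed below 80%. The wording needs clarifying, no more.
- A reader might infer that question 2 is defeated because all reported compliance must be at least 80%. Only attendance is cut off at that level. Compliance is also assessed at monthly contacts for nine months, diet and exercise compliance can take any value, and reasons for dropout are recorded.
- A reader might infer that the cost of delivering CHIP to people who stop attending is lost. The protocol counts costs attributed to the project and does not say that these fall when a participant is excluded.
- A reader might set the bias, converted with the stated SD of 20, against the planned 3.5. That figure is a percentage reduction, and neither a baseline mean nor a unit for the SD is given, so the comparison is not supported.

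**Conclusion.** The point holds. As written, the protocol removes participants from one randomised arm on the basis of behaviour after allocation, and the planned between-group test would then compare CHIP attenders with controls not selected by attendance. That is a defect in the main comparison whatever the numbers turn out to be.

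Its size is not known. At the protocol's own 10% dropout figure the illustration gives a modest effect, with type I error of 5.6% to 7.5%. It becomes serious at 20% (7% to 13%) and 30% (9% to 20%). These figures rest on the assumed correlation and exclusion rates.

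It is tempting to say that the results will be biased in favour of CHIP. That direction is likely, because people who stop attending plausibly have worse glucose control, but the documents do not establish it. Questions 2 and 3 are weakened rather than made unanswerable. The change should be made before recruitment starts, since outcomes that are never collected cannot be restored.

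**What to change.** - In the Group 1 section, delete the clause that excludes low attenders from the study. They can still be recorded as having dropped out of the intervention.
- Invite every randomised participant to the 12-week and 12-month assessments whatever their attendance, unless they withdraw.
- Make analysis by randomised arm the primary analysis for questions 1 and 3.
- Report attendance for all of Group 1 under question 2.
- Use the 80% threshold only in a secondary adherence analysis that is labelled as such. Write it as a number of the 18 sessions, and say whether the four sessions are sessions missed.

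The cost is small: a change of wording, and completing for low attenders two assessments that were already planned for both groups. The estimated effect may be smaller than one in attenders alone, but it would be the effect of offering the programme, which is what the funding question needs.

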#### Group 2 – control group

The control group will continue to receive their usual diabetes care and not receive any intervention or details about the CHIP intervention.

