The Complete Health Improvement Program (CHIP) is a lifestyle intervention that was primarily designed to reverse coronary artery disease (CAD). Since its inception in 1988, researchers have become increasingly aware that the intervention was also effective in improving clinical outcomes for diseases like hypertension and T2DM. More than 30 published papers have indicated that the CHIP intervention leads to dramatic improvement in the indicators of these diseases of lifestyle. [14–17].

With no known medical cure for T2DM as well as the current and predicted increasing prevalence of the disease, it is important that the benefits of improved lifestyle in the population with diabetes continue to be explored. Increasing healthcare costs associated with chronic diseases and their complications make it necessary to employ programs that are effective and demonstrate a cost benefit.

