### Study participants

Patients, who have a diagnosis of T2DM will be recruited from general practice medical centers (where practitioners have agreed to refer) on the Central Coast of NSW, Australia. Recruited patients will be invited to participate in the study. Enrollment of consenting participants will continue until the required sample size is met. The source population will be monitored at each participating General medical practice in order to ascertain what percentage of diabetes patients would be suitable to join the programme. Potential participants will be excluded based on the criteria below.

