### Exclusion criteria

Persons will be ineligible for the study if:they are aged less than 18 yearsthe consulting medical practitioner considers that an alteration in nutrient or calorie consumption or that participating in regular moderate exercise could result in an increased health risk. This may include but may not be limited to:i.persons having a history of uncontrolled hypertension with consistent resting blood pressure readings greater than 180 mmHg systolic and or greater than 110 mmHg diastolic;ii.persons having a BMI lower than 21 kg/m^2^, and making use of weight-loss medication;iii.persons experiencing recurrent chest pain or unstable angina;iv.pregnant or lactating females, or females planning to become pregnant in the next year;v.persons who have undergone angioplasty or experienced a myocardial infarction or cardiac surgery within the previous three months;they have any condition that precludes them from increasing their level of physical activity;they have any physical condition or language barrier that would preclude them from understanding or safely adopting the lifestyle changes recommended by the CHIP intervention.

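### The exclusion list and individual randomisation do not protect the control condition when participants share a household, and they admit past CHIP attenders; worth a cheap fix, size unknown and probably small

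*Protocol article*

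**What the plan says.** All references are to the protocol article.

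- **Control condition** (Group 2 – control group): controls stay on usual diabetes care and will "not receive any intervention or details about the CHIP intervention".
- **Source** (Study participants): patients "will be recruited from general practice medical centers (where practitioners have agreed to refer) on the Central Coast of NSW, Australia".
- **Basis for exclusion** (Study participants): "Potential participants will be excluded based on the criteria below". The list that follows covers age under 18, health risk as judged by the practitioner, inability to be more active, and "any physical condition or language barrier that would preclude them from understanding or safely adopting the lifestyle changes". The open-ended phrase "This may include but may not be limited to" belongs to the health-risk item only.
- **Allocation** (Allocation of participants to a study group): once 30 to 40 volunteers are listed, "the individual participants will be randomized into either Group 1 or Group 2". The process repeats until 150 are enrolled. No household rule is stated, and the Randomisation section says the trial is unblinded.
- **Content** (Group 1 – intervention group): the sessions contain group activities, "including food preparation and exercise demonstrations delivered by CHIP trained volunteers", and encourage a plant-based diet low in sugar and salt.
- **History** (Background): "Since its inception in 1988, researchers have become increasingly aware that the intervention was also effective".

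**The concern.** The article fixes three things: what controls must not get, who is kept out, and the unit of randomisation. The second and third do not secure the first. Cooking and diet are easily shared at home, so a control who lives with a Group 1 participant may pick up part of the intervention. The plan as written allows this pairing.

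A different matter is the person who completed CHIP before the trial. The programme dates from 1988 and nothing in the exclusion list keeps such a person out. In Group 1 that person has less left to gain.

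What is at stake is the contrast between arms in glucose, lipids, weight and cost. Either route can bias it towards no difference. The limitations section discusses compliance, self-report and the Hawthorne effect, but not this.

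**Working it through.** **1. Can the plan as written produce the situation?** The exclusion list is stated to be the basis for exclusion, and neither a shared household nor past attendance is on it. The unit of randomisation is the individual. With 150 participants and lists of 30 to 40, there are 150/40 = 3.75 to 150/30 = 5 lists, so four or five. Cohabiting patients can be split within one list or across two. The answer is yes for both routes.

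**2. Size, household route.** Let p be the share of controls exposed and f the fraction of the CHIP effect they gain. With true effect Δ, the observed difference is Δ − p·f·Δ = Δ(1 − p·f). The sample size needed for the same power rises by 1/(1 − p·f)². The documents give neither p nor f, so the values below are assumptions.

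The plan's own sample size cannot serve as the base. A difference of 3.5 with SD 20, two-sided 5% and 80% power needs 2 × (1.960 + 0.842)² × 20²/3.5² ≈ 513 per arm before dropout, not 75 including dropout. That is a separate matter. The power column therefore takes as given that the trial would have 80% without dilution: power = Φ(2.802 × (1 − p·f) − 1.960).

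| p (of 75 controls) | f | Loss p × f | Sample inflation | Power, if 80% undiluted |
|---|---|---|---|---|
| 2/75 = 2.7% | 0.5 | 1.3% | 1/0.9867² = 1.027 | Φ(0.804) = 78.9% |
| 5% (3.75 people) | 0.5 | 2.5% | 1/0.975² = 1.052 | Φ(0.772) = 78.0% |
| 10% (7.5 people) | 1 | 10% | 1/0.90² = 1.235 | Φ(0.562) = 71.3% |

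**3. How plausible are these rows for households?** Individual 1:1 randomisation splits a couple about half the time, so each split couple implies about two enrolled couples.

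- Row 1: about 4 couples, or 8 of 150 participants.
- Row 2: about 7.5 couples, or 15 of 150.
- Row 3: about 15 couples, or 30 of 150, each person with diagnosed T2DM, eligible and consenting. It also needs every exposed control to gain the full effect without attending.

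Row 3 is an outer bound, not an expectation.

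**4. Size, past-attender route.** Past benefit is already in the baseline values, so these controls do not improve further during the trial. The mechanism is a smaller gain in Group 1. If a share q of each arm has already gained a fraction g, the Group 1 gain is (1 − q)Δ + q(1 − g)Δ = Δ(1 − q·g), while the control change is unaffected. Randomisation balances past attenders between arms in expectation, but the factor (1 − q·g) remains. No value of q or g is given.

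**The case against.** The case on the other side is strong on several points.

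- **Past attendance contradicts nothing.** The control-group section describes what controls receive in the trial, not what they did in earlier years. This stands. A reader might infer that enrolling a past attender breaks the plan's own requirement; the text does not support that. What remains is a smaller contrast.
- **Nothing shows that such people exist here.** The article gives no count of past attenders or couples and does not say CHIP ran on the Central Coast before; the community halls it names are the trial's own venues. This stands. A reader might infer that the effect is diluted as a matter of fact; the documents support only that it can be.
- **Sharing meals is not receiving CHIP.** The programme is 18 sessions, about half of each being video, with topics well beyond food, followed by nine months of monthly contact. This stands, and it makes f = 1 unlikely.
- **Exposure could be recorded instead.** Diet and activity surveys are taken in both groups, so dietary drift in controls would be partly visible. A reader might infer that the analysis could not recover anything because these items are not exclusions; that does not follow, since recovery depends on what is recorded. But the data items listed do not include past CHIP attendance or household links, so drift could not be traced to its source from them.
- **This is a condensed article.** The full protocol may hold a further criterion. This is possible, but the article presents its list as the basis for exclusion and states its unit of randomisation.

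**Conclusion.** The point holds as a low-cost improvement, not as a demonstrated flaw in the result. On the stated criteria, a control may live with a Group 1 participant, which sits badly with the control condition, and a past attender may enter either arm, which does not conflict with it but reduces what can be gained. Both act towards zero. For the household route, the assumed values give a loss of about 1.3% to 2.5% of the effect, equivalent to about 3% to 5% more patients; 10% is an unlikely upper case. For past attenders no size can be given. All of this rests on assumed values of p and f, and on the full protocol containing no further rule.

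**What to change.** Make two additions to the exclusion criteria:

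1. Exclude anyone who has previously taken part in a CHIP programme.
2. Enrol at most one person per household across all lists. Someone who lives with a person already randomised is not eligible. If two people from one household are on the same list, one is chosen before randomisation by a rule set in advance.

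Do not allocate couples together as a unit. That creates clusters, while the planned between-group comparison is an independent t-test that treats participants as independent.

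The cost is two screening questions and an amendment, which is easy at the stage the article reports, with recruitment about to begin and nobody enrolled. The downside is the loss of a few otherwise eligible patients.
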